## 2. Materials and Methods

### 2.1. Study Design

This is a cross-sectional, vignette-based experiment with a four-level within-subjects (repeated-measures) design. Vignette experiments combine the internal validity of experimental manipulation with survey feasibility and are an established method for isolating drivers of health-related judgments [61]; their design and analysis follow current methodological guidance for vignette data [62]. Each participant reads and evaluates all four scenarios of AI implementation (A–D), presented in a counterbalanced sequence. The within-subjects structure makes each respondent their own control, eliminating inter-individual variability from between-scenario comparisons and substantially increasing statistical power relative to a between-subjects design of the same size [63]. The presentation sequence is counterbalanced. The survey platform allocates participants at random, in equal proportions and independently of any participant characteristic, to one of the four sequences of a Williams (balanced Latin-square) design: A → B → C → D, B → D → A → C, C → A → D → B, and D → C → B → A. In this square, every scenario occupies every serial position exactly once, and every ordered pair of scenarios occurs exactly once, so that autonomy level is orthogonal both to serial position and to first-order carry-over, and an additive model containing a four-level autonomy effect and a four-level serial-position effect is fully identified. The theoretically motivated ascending sequence and its exact mirror image are retained as two of the four arms. A fixed ascending presentation would have mirrored the progressive continuum under investigation and given every participant an identical evaluation context, but it would have left order, carry-over, and fatigue effects inseparable from the autonomy gradient; because H1–H3 concern precisely that gradient, internal validity was given priority over uniformity of context. Counterbalancing also makes the embedded manipulation check diagnostic rather than merely descriptive: perceived AI control should track the described autonomy level within every sequence, whereas an anchoring or fatigue artifact would instead track serial position—a distinction that a monotonic manipulation-check profile obtained under a fixed order cannot draw. Presentation sequence is therefore retained as a between-subjects factor in all primary models, a second manipulation check (perceived technical sophistication) separates autonomy from technical complexity, and a per-scenario difficulty item indexes fatigue (Section 2.6, Section 2.7, Section 2.8, and Section 2.9.1). The study involves no medical, pharmacological, or surgical intervention. Reporting of the completed study will follow current recommendations for effect-size-based reporting [64] and, for the web-survey component, the CHERRIES checklist as operationalized in recent methodological guidance [65]. Publication of the protocol in advance of data collection is intended to reduce publication bias and analytic flexibility [66,67].

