### 2.5. Sample Size and Power

Sample size is justified a priori following current recommendations [70], with all calculations derived analytically from noncentral *F*, t, and chi-square distributions at a two-tailed significance threshold of α = 0.05 and a target power of 1 − β = 0.80, reproducible in G*Power 3.1 (“ANOVA: Repeated measures, within factors”) and consistent with recent tutorials on power analysis for repeated-measures designs [63]. The primary test is a repeated-measures ANOVA (four within-subject levels) on each composite score. Assuming a correlation between repeated measurements of ρ = 0.50 (a typical value for repeated attitudinal ratings, to be verified in the pilot), the minimum sample is 24 participants for medium effects (*f* = 0.25) and 138 for small effects (*f* = 0.10); under the conservative assumption ρ = 0.30, these become 32 and 193, respectively. The minimum analyzable threshold is therefore set at *N* = 140 valid participants, sufficient to detect even small between-scenario effects under realistic conditions. Because these thresholds depend on ρ, an adaptive rule is pre-registered for the case in which the pilot estimate falls outside the assumed ρ = 0.30–0.50 range. The pilot returns $\hat{\rho }$ with a 95% confidence interval, and every threshold is recomputed at its lower bound, ρ_L_, which is the conservative choice. The number of valid participants required to detect *f* = 0.10 at power 0.80 is 274, 247, 220, 193, 165, and 138 for ρ_L_ = 0, 0.10, 0.20, 0.30, 0.40, and 0.50, respectively; an intermediate ρ_L_ is rounded down to the nearest tabulated value, so that the rule is fully determined in advance for any estimate the pilot can return. Two consequences follow. The recruitment target does not change because the requirement is a decreasing function of ρ and reaches only 274 in the theoretical worst case of ρ_L_ = 0; *N* = 300 preserves power ≥0.80 against small between-scenario effects for every value ρ can take, and the target is in any case set by the person-level analyses described below, which do not depend on ρ. The analytic floor does change: it is redefined as the value tabulated above for the observed ρ_L_, so that it remains at the pre-specified *N* = 140—rounded up from 138—only when ρ_L_ ≥ 0.50 and rises to 165, 193, 220, 247, or 274 as ρ_L_ falls to 0.40, 0.30, 0.20, 0.10, or 0. A ρ_L_ below 0.10 would in addition indicate that the composites are unstable across repetitions rather than that participants are inconsistent, and would therefore also trigger re-inspection of pilot reliability and of the measurement-invariance assumptions before the main study is launched. Any application of this rule, and the $\hat{\rho }$ that triggered it, will be recorded in the pre-registration and reported in the results article.

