
The recruitment target is *N* = 300 valid participants. This target is dictated not by the within-subjects effects (for which power at *N* = 300 is 0.99 for small effects at ρ = 0.50, with a minimum detectable effect of *f* = 0.07), but by the person-level analyses: the familiarity moderation (minimum detectable interaction *f*^2^ = 0.037 at *N* = 300), the global preference test (minimum detectable *w* = 0.21 on 5 degrees of freedom), and descriptive analyses of demographic subgroups. A small interaction effect (*f*^2^ = 0.02) would require *N* ≈ 550; H4 therefore remains partially exploratory, and a non-significant result will not be interpreted as evidence of absence. At *N* = 300, dependent pairwise comparisons detect differences from *dz* = 0.16 (uncorrected) and *dz* = 0.20 (at the Bonferroni bound for six pairwise comparisons), so all six scenario contrasts can be treated as confirmatory. Counterbalancing entails no loss of sensitivity for the primary comparisons: with sequence entered as a four-level between-subjects factor, the autonomy main effect retains 3 degrees of freedom and the same noncentrality, so the minimum detectable effect at *N* = 300 remains *f* = 0.07. The scenario × sequence interaction—the direct test of order dependence—carries 9 degrees of freedom and a minimum detectable effect of *f* = 0.08 at ρ = 0.50 (*f* = 0.10 at ρ = 0.30), giving power of 0.95 against a small order effect of *f* = 0.10; the serial-position main effect in the additive model carries 3 degrees of freedom and matches the sensitivity of the autonomy effect itself. Order artifacts large enough to masquerade as the hypothesized autonomy gradient are therefore detectable, rather than being assumed away. In the pilot, by contrast, the ascending and descending arms (*n* = 25 each) bound order effects only at *f* = 0.17, which excludes medium-to-large artifacts but not small ones; the definitive test is the main-study interaction. Table 2 summarizes the power analysis, and Figure 1 shows achieved power as a function of the number of valid responses.

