
### 2.8. Pilot Study and Instrument Validation

The instrument will be validated in a pilot study (*N* = 50, not included in the main sample, allocated 1:1 to the ascending sequence A → B → C → D and to its exact reverse D → C → B → A) before the main study is launched. The pilot will estimate (i) internal consistency—Cronbach’s α and McDonald’s ω with 95% confidence intervals for each three-item composite, computed separately per scenario, against a threshold of ≥0.70, with ω reported alongside α in line with current psychometric guidance [73]; with three items per construct, α ≥ 0.70 requires a mean inter-item correlation of only $\bar{r}$ ≥ 0.44 under the generalized Spearman–Brown relation (Figure 2), a realistic requirement for parallel items; (ii) inter-item correlations (flagged at r > 0.90 for redundancy or r < 0.20 for heterogeneity) and corrected item-total correlations (threshold ≥ 0.40), plus the correlation between repeated measurements, reported with a 95% confidence interval, to verify the ρ ≈ 0.50 planning assumption and, where it is not met, to trigger the adaptive sample-size rule of Section 2.5; (iii) the factor structure of the nine response items, via exploratory factor analysis (principal-axis extraction, oblique rotation, sampling adequacy KMO ≥ 0.70, Bartlett’s test of sphericity, parallel analysis as the retention criterion)—an anticipated risk is that acceptability and trust items form a single factor, in which case the two constructs will be merged into a single “trust–acceptance” score and the analysis plan adjusted transparently before pre-registration, with this decision taken exclusively on pilot data; (iv) first-attempt comprehension-check pass rates per scenario (threshold ≥ 70%); (v) manipulation validity—MAN1 scores must order the scenarios from A to D in both pilot arms, while MAN2 (perceived technical sophistication) must not increase monotonically with autonomy; if it does, the vignettes will be reworded to equalize the described sophistication of the systems and the check repeated before pre-registration; (vi) fatigue—perceived difficulty (DIF1) and section-wise drop-out across serial positions in both arms; (vii) cognitive interviews with 5–8 participants to identify confusing wording, probing in particular whether RES1–RES6 are read in the intended senses of moral answerability, outcome-independent accountability, and legal fault (Section 2.6); and (viii) a first bound on order effects—the two pilot arms are compared on the three composites and on MAN1 by a scenario × order mixed ANOVA (*n* = 25 per arm; minimum detectable interaction *f* = 0.17 at ρ = 0.50), which can exclude medium-to-large order artifacts but not small ones, the definitive test being the main-study interaction. The four-sequence randomizer used in the main study is implemented in the same pilot build. Because the pilot itself exercises only two of the four arms, the randomizer is verified there by simulated allocation, which also confirms that the allocated sequence and the serial position of each scenario are stored correctly. A ninth objective is included: (ix) the keying and dimensionality of the four general-attitude items (G1–G4), since G3 is a caution item that the present scoring treats as positively keyed while G2 and G4 are reversed; the scoring rule for that block is fixed on pilot data before pre-registration, and if the four items do not form a single interpretable dimension they will enter the person-level analyses individually rather than as a composite. Because a sample of 50 is at the lower limit for stable factor solutions, the pilot EFA is treated as provisional: the factor structure will be re-examined by confirmatory factor analysis on the main sample (*N* = 300), with acceptable fit defined a priori as CFI/TLI ≥ 0.95, RMSEA ≤ 0.06, and SRMR ≤ 0.08. Because the same nine items are answered four times, longitudinal measurement invariance across the four scenario repetitions (configural, metric, and scalar) will also be tested on the main sample; at least partial scalar invariance is required for the between-scenario comparison of composite means, and any non-invariant item will be reported and handled by partial-invariance modeling. Pilot results will be reported in the methods section of the results article.

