Scenario × sequence interaction—order test (*df* = 9)	*N* = 300, ρ = 0.50	*f* = 0.08
Scenario × sequence interaction—order test (*df* = 9)	*N* = 300, ρ = 0.30	*f* = 0.10
Pilot order bound, ascending vs. descending arm (*df* = 3)	*N* = 50, ρ = 0.50	*f* = 0.17
Dependent comparison within a demographic subgroup	*n* = 50, α = 0.05	*dz* = 0.40

Abbreviations: RM-ANOVA, repeated-measures analysis of variance; *N*, number of valid participants; *n*, number of participants per pilot arm or subgroup; ρ, correlation between repeated measurements; α, significance threshold; *df*, degrees of freedom; f and *f*^2^, Cohen’s effect-size indices for *F* tests; *dz*, Cohen’s effect size for dependent-samples comparisons; *w*, effect size for the goodness-of-fit chi-square test.

**Table 3 healthcare-14-03030-t003:** Projected recruitment funnel.

Stage	Assumed Pass Rate	Estimated Number
Link accesses	—	≈545
Begin questionnaire (consent given)	85% of accesses	≈463
Eligible after screening (items S1, S2)	96% of starters	≈445
Completed (submitted) questionnaires	75% of eligible	≈334
Valid after quality exclusions (ATT, CC, invariant, duplicates)	90% of submitted	≈300

Abbreviations: S1 and S2, the two screening items of the instrument (Appendix A.1); ATT1 and ATT2, attention checks; CC_A–CC_D, comprehension checks.

**Table 4 healthcare-14-03030-t004:** Measurement structure of the instrument.

Construct/Variable	Items	Scale	Role in Analysis
Acceptability	ACC1–ACC3 (mean), per scenario (×4)	Likert 1–7	Primary DV (H1), within-subjects
Trust	TRU1–TRU3 (mean), per scenario (×4)	Likert 1–7	Primary DV (H1), within-subjects
Perceived risk	RSK1 (reversed), RSK2, RSK3 (mean), per scenario (×4)	Likert 1–7	Primary DV (H2), within-subjects
Responsibility attribution	RES1–RES4, per scenario (×4)	Likert 1–7	Secondary DV (H3), within-subjects
Responsibility principles	RES5, RES6, per scenario (×4)	Likert 1–7	Secondary DV
Global preference	P1	7 response options (6 analysis categories)	Secondary DV
General acceptability	P3	Likert 1–7	Secondary DV
AI familiarity	B1	Likert 1–7	Moderator (H4)/covariate
General AI attitudes	G1–G4 (G2, G4 reversed)	Likert 1–7	Covariates
Experience and demographics	B2–B5, D1–D7	Mixed	Covariates/sample description
Manipulation check (perceived AI control)	MAN1, per scenario (×4)	Likert 1–7	Design validation
Scenario difficulty	DIF1, per scenario (×4)	Likert 1–7	Control covariate (fatigue)
Data quality	ATT1, ATT2, CC_A–CC_D	Categorical	Exclusion criteria

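### The pilot's two mirror-image sequences cannot detect order effects symmetric about mid-sequence, yet the protocol says the pilot test excludes medium-to-large order artifacts

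*Protocol article*

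**What the plan says.** Section 2.8 allocates the pilot (N = 50) to two sequences only: "allocated 1:1 to the ascending sequence A → B → C → D and to its exact reverse D → C → B → A". Objective (viii) of that section compares the two arms on the three composites and on MAN1 with a scenario × order mixed ANOVA, with "25 per arm; minimum detectable interaction *f* = 0.17 at ρ = 0.50". It describes this as a test "which can exclude medium-to-large order artifacts but not small ones, the definitive test being the main-study interaction". Section 2.5 repeats the claim: the pilot arms give a bound "which excludes medium-to-large artifacts but not small ones; the definitive test is the main-study interaction". Table 2 carries the same f = 0.17 with 3 degrees of freedom. In both sections the only limit placed on the claim is the size of the effect.

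The main study uses four sequences: "A → B → C → D, B → D → A → C, C → A → D → B, and D → C → B → A". Section 2.1 justifies them because a four-level position effect can then be separated from a four-level autonomy effect. Section 2.8 notes that the pilot lacks two of these arms, but only in connection with checking the software: "Because the pilot itself exercises only two of the four arms, the randomizer is verified there by simulated allocation".

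**The concern.** In the two pilot arms, scenarios A and D are only ever read at positions 1 and 4, and B and C only at positions 2 and 3. A position effect that treats the two ends alike and the two middle positions alike, such as warm-up followed by fatigue, is therefore the same for each scenario in both arms. The arms cannot disagree about it, so the interaction cannot show it.

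This matters because some pilot decisions are locked before pre-registration (Section 2.12), among them whether the vignettes are reworded. One rewording trigger is MAN2: the vignettes are revised only if perceived sophistication rises monotonically from A to D. The pilot order test covers the composites and MAN1, not MAN2. A symmetric position effect on MAN2 would change the profile being judged, and nothing in the pilot would reveal it. The main study can reveal it, but only once the wording is fixed.

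**Working it through.** **Inputs.** Pilot N = 50, two arms, m = 4 scenarios, ρ = 0.50 (Section 2.8). Testing is "at a two-tailed significance threshold of α = 0.05 and a target power of 1 − β = 0.80" (Section 2.5). Main-study sequences are from Section 2.1.

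**Step 1: reproduce the plan's figure.** For a within-between interaction, λ = f²·N·m/(1−ρ), df1 = (m−1)(g−1), df2 = (N−g)(m−1), where g is the number of arms. With g = 2, df = (3, 144) and λ = f² × 50 × 4/0.5 = 400f². Power 0.80 is reached at f = 0.167, and power at f = 0.17 is 0.814. The stated 0.17 reproduces. So do the main-study order figures: f = 0.081 at ρ = 0.50, f = 0.096 at ρ = 0.30, and power 0.952 at f = 0.10.

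**Step 2: what the interaction contains.** Let p1 to p4 be additive serial-position effects. For scenarios (A, B, C, D):

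- ascending arm: (p1, p2, p3, p4)
- descending arm: (p4, p3, p2, p1)
- difference between arms: (p1−p4, p2−p3, p3−p2, p4−p1)
- mean of the arms: ½(p1+p4, p2+p3, p2+p3, p1+p4)

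If p1 = p4 and p2 = p3, the difference is (0, 0, 0, 0), and the whole effect goes into the scenario means as A/D against B/C.

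| Position effect | Two arms: share in interaction | Two arms: share in scenario main effect | Four sequences: share in interaction |
|---|---|---|---|
| linear (−3, −1, 1, 3) | 100% | 0% | 100% |
| cubic (−1, 3, −3, 1) | 100% | 0% | 100% |
| symmetric (1, −1, −1, 1) | 0% | 100% | 100% |
| first position only (1, 0, 0, 0) | two thirds | one third | 100% |

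As a cross-check, the model sequence + scenario + position needs 8 independent parameters in the pilot (2 + 3 + 3), and its design matrix has rank 7. In the Williams square it needs 10 (4 + 3 + 3) and has rank 10.

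**Step 3: simulated rejection rates** (4000 replicates per cell, ρ = 0.50).

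| f | Linear, two arms of 25 | Symmetric, two arms of 25 | Symmetric, four arms of 13 (9-df interaction) |
|---|---|---|---|
| 0.17 | 0.818 | 0.051 | 0.636 |
| 0.25 | 0.991 | 0.052 | 0.964 |
| 0.40 | 1.000 | 0.056 | 1.000 |
| 0.80 | 1.000 | 0.049 | 1.000 |

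With no autonomy effect at all, a symmetric position effect of f = 0.25 gives λ = 400 × 0.0625 = 25. The pilot's scenario main effect would then be significant with probability 0.99.

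**Step 4: the other pilot checks.** Write a symmetric effect as (0, δ, δ, 0).

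- MAN2: the observed D−C step becomes the true step minus δ, in both arms. If δ exceeds the true D−C gap, a truly rising profile looks non-monotone and passes. With δ negative, a true C above D can be hidden.
- DIF1 by position: positions 1 and 4 each hold A in one arm and D in the other, so first against last is balanced. The same holds for positions 2 against 3. Only {1, 4} against {2, 3} is aliased, with {A, D} against {B, C}.

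**Step 5: four sequences with N = 50.** In the additive autonomy + position model, the error df are 150 − 3 − 3 = 144, so the 3-df position test has the same minimum detectable effect, f = 0.167, for every position shape. The 9-df scenario × sequence interaction (error df 138) has f = 0.204.

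**The case against.** The pilot is called a first bound, its participants are kept out of the main sample, and the main-study test over four sequences is named as definitive. The order bound is not among the pilot decisions that Section 2.12 locks. The two-arm choice also targets the most relevant threat. An order effect that mimics the hypothesized gradient must have a linear part, and linear and cubic effects fall wholly in the pilot interaction. The symmetric pattern has no linear component: (1)(−3) + (−1)(−1) + (−1)(1) + (1)(3) = 0. All of this stands. It limits the consequence, but calling the result a first bound qualifies its size and not its shape.

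A reader might infer more than the documents support:

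- **The main study's order control fails.** It does not; the Williams square identifies arbitrary position effects.
- **The MAN1 ordering could be manufactured.** A shift of (0, δ, δ, 0) leaves C−B and D−A unchanged and takes from D−C what it adds to B−A. It cannot turn a flat profile into an A-to-D ordering.
- **The pilot ρ, and so the analytic floor, is biased.** Every four-position sequence has three pairs one step apart, two pairs two steps apart and one pair three steps apart. If correlation depends additively on scenario pair and distance, the six-pair mean is the same in all sequences. No direction or size of bias can be derived.
- **Unacceptable fatigue could pass a gate.** Section 2.8 sets no acceptance threshold for DIF1 or drop-out.
- **First-item effects escape.** One third of the variance is lost, so the minimum detectable effect rises to 0.1674/√(2/3) = 0.205, still below medium (0.25).

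**Conclusion.** The statement in Sections 2.5 and 2.8 is wrong for one class of order effect. For additive position effects symmetric about the middle of the sequence, the pilot test has power equal to α whatever the size, so medium and large artifacts of that shape are not excluded. The same effect shifts the pilot MAN2 check unseen and aliases one of the three DIF1-by-position comparisons. Linear and cubic order effects are bounded as the plan says, and no confirmatory analysis is affected.

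The result is exact for additive serial-position effects. Carry-over or scenario-specific order effects could still register in the two-arm interaction. The documents do not show that a symmetric effect will occur, and the MAN2 example needs one larger than the true D−C gap. The point is that the plan claims to exclude such effects and cannot. It should be corrected before the pilot starts.

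**What to change.** Either of two changes resolves it.

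1. **Use all four Williams sequences in the pilot.** Allocate the 50 participants 12–13 per sequence with the randomizer already in the pilot build. Test order as the 3-df serial-position effect in the additive autonomy + position model (minimum detectable f = 0.167 at ρ = 0.50), and report the 9-df scenario × sequence interaction beside it (f = 0.204). Judge MAN1 and MAN2 on position-balanced means, and keep the within-sequence MAN1 ordering as a descriptive check so that this diagnostic is not lost. This needs no extra participants and tries all four sequences on people. The costs are noisier sequence profiles, a wider bound for the full interaction (0.204 against 0.167), and a 3-df test that assumes no carry-over.

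2. **Keep two arms and restate the claim.** In Sections 2.5 and 2.8, and in the Table 2 row, say that the pilot bounds only order effects that reverse with the sequence and gives no information on effects symmetric about its middle. Note the same limit for the MAN2 check and for DIF1 by position. This costs a few sentences but leaves the MAN2 rewording decision exposed.
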